# 1 INTRODUCTION

## 1.1 Scientific background

Asthma is the most common chronic disease in children, imposing a high lifetime burden on individuals, their caregivers, and healthcare systems (1, 2). The prevalence of childhood asthma has increased over the last 20 years, most likely due to a greater awareness of this condition and changes in diagnostic practice. In Germany, parent-reported asthma prevalence in preschool children (< 6 years) ranged from 2.6 to 2.8% (3).

As in adults, a considerable proportion of asthma in children is not well controlled by inhaled corticosteroids (ICS), which represents a significant healthcare concern (4). Failure to control asthma has a negative impact on patients' quality of life, and increases the risk of future exacerbations, with associated increased requirement for healthcare utilization and costs (5, 6).

The global prevalence of diagnosed current asthma in children 5 years and younger cannot be estimated well due to the lack of international consensus on the diagnostic criteria. Asthma is, however, the most common chronic disease of childhood with a significant impact on the pediatric health care resource utilization for asthma management by children below 5 years of age despite current treatment (7, 8). Asthma typically begins in early childhood and is generally diagnosed more often in boys than girls (8, 9). Atopy is present in the majority of children with asthma over the age of 3, and allergen-specific sensitization is one of the most important risk factors for the development of asthma (10).

Of note is the diagnostic uncertainty among young children in whom wheezing is more likely to be associated with lower respiratory tract infection, and often is transient (9, 11–13). Although the asthma prevalence of school children is higher than in toddlers, severe asthma exacerbations with emergency visits and hospital admissions are disproportional more often in preschool asthma (14–16). In addition, young children have increased vulnerability to adverse outcomes due to small airways and possibly increased bronchial airway reactivity, in comparison with older children (17). Respiratory distress in the setting of infection can rapidly become life-threatening. For this reason, the relatively high utilization of emergency visits and hospital admissions in preschoolers may be well explained. A retrospective analysis of the electronic medical records at the Department for Children and Adolescents, Goethe University showed a significant number of acute asthma admissions (approximately 60 new cases annually) in this age group, 1–5 years. In addition, re-admissions with acute asthma exacerbations were surprisingly high with approximately 20%, despite frequent hospital discharge with asthma control therapy like inhaled corticosteroids (ICS) and leukotriene receptor antagonist (LTRAs) (18). This is much higher than in a study in England showing 5% and more close to the range of a recent report in France with 15% re-admission rates (18–20). Early intervention with anti-inflammatory agents is indicated in preschool asthma to prevent the development of uncontrolled asthma and frequent exacerbations with high health care utilization (16, 21, 22). Although studies are limited, data suggest that an asthma-like inflammation (presence of eosinophils and allergic sensitization) may be present at a very early age in some children with recurrent wheeze (16, 23). Currently available anti-inflammatory treatments for first-line therapy in preschool asthma include ICS and LTRAs. Both ICS and LTRAs have been found to be effective in this age group (24–27). Sensitization and eosinophils are useful in the prediction of future exacerbation and may identify children most

likely to respond favorably to daily ICS treatment (16, 23, 27). ICS is effective to reduce severe exacerbations by only 36% in preschool asthma patients (16, 27). Thus, asthma exacerbations occur frequently despite the regular use of ICS. Optimizing asthma management among preschool children by quintupling the ICS dose at the early signs of loss of asthma control did not reduce the rate of severe asthma exacerbations and may be associated with diminished linear growth (28). In addition, in children with persistent asthma, the addition of long-acting beta-agonists (LABA) to ICS was not associated with a significant reduction in exacerbations requiring systemic steroids (29, 30).

Currently, short-acting Ipratropium is a widely used treatment of patients with preschool asthma as a reliever in acute wheezing. According to the results of Beck R, et al. (31), a beneficial effect of the short-acting anticholinergic Ipratropium as inhalation added to the standard care could be shown. As Tiotropium offers a superior time-response profile as a bronchodilator to Ipratropium, it is likely to be more effective and has sustained anti-obstructive effects for 24 hours in children 1–5 years with asthma. The 24-hour duration of action profile may be of special value in toddlers suffering from nocturnal events of e.g., shortness of breath, which is the case in moderate and severe but still not optimally controlled asthma. The ease of use taking a drug only once daily could also enhance compliance of the younger patient population.

Tiotropium in the Respimat® inhaler is the first long-acting muscarinic antagonist licensed for treatment of asthma and effective as add-on therapy to ICS in patients aged 6 years and older with severe asthma who experienced one or more severe asthma exacerbations in the preceding year. Tiotropium was found to be well-tolerated and efficacious add-on to ICS plus one or more controller medications in many clinical trials in children (32–36). Its therapeutic success in clinical trials resulted in Food and Drug Administration and the European Medicines Agency (EMA) approval for asthma treatment in people aged  $\geq 6$  years in the US and EU. GINA strategy includes the addition of long-acting muscarin receptor antagonist (LAMA) at Step 4–5 as an add-on to ICS + LABA treatment for patients aged  $\geq 6$  years, before escalation to treatment with biologics or low-dose oral corticosteroids (37). Interestingly, Tiotropium might also be relevant as an asthma control therapy, since there is preliminary evidence that it not only functions as a bronchodilator through inhibition at the muscarinic M3 receptors but also has anti-inflammatory properties (38). In addition, Tiotropium has been shown to be efficacious regardless of IgE levels and blood eosinophils and might therefore be especially interesting in preschool asthma (16, 39, 40) since the percentage of preschool children with asthma with elevated IgE levels and/or significant eosinophilia is lower than in school asthma. Thus, adding Tiotropium to ICS might be a new promising treatment option for severe uncontrolled preschool asthma (41, 42).

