| SECONDARY ENDPOINTS  | 
Key secondary endpoint(s): number of severe exacerbations, number of hospitalizations (severe exacerbation), (severe) exacerbation-free survival time, number of asthma-related events defined by use of antibiotics, percentage of night-time awakenings due to asthma symptoms as assessed by the electronic patients diary/PACD, percentage of days without asthma symptoms assessed by TIPP diary App (PACD), , percentage of days and episodes of > 3 days with use of PRN salbutamol rescue medication, health utilization (number of physician visits), number of missed days in daycare, result of TRACK, CGI-C at end of treatment and potential biomarkers for treatment response:
 
Eosinophils, IgE, specific IgE to common allergens (birch, grass, Dermatophagoides pteronyssinus, Alternaria, Cladosporium, cat, dog, hen's egg, cow's milk and peanut.
 
Assessment of safety:
Safety will be ensured by analysis of symptom scores and rescue medication use by the electronic diary, and adverse events (AEs).
                                                                                                                                                  |
| STATISTICAL ANALYSIS | 
Efficacy:
The comparison between groups will be made by time to first severe exacerbation within 12 months of therapy.
 
Description of the primary efficacy analysis and population:
The time to first severe exacerbation will be analyzed by Cox regression with factor treatment and the covariates age group and center. Analyses will be performed in the intention-to-treat population and repeated in the per-protocol population as sensitivity analyses. Treatment differences will be displayed by hazard ratios and 95% confidence intervals.
 
Safety: For safety analyses, frequencies of patients experiencing at least one adverse event (AE) will be displayed by system organ class and preferred term according to MedDRA terminology.
 
Secondary endpoints:
For secondary analyses, Cox regression for time to event data will be used and negative binomial regression for count of events. Further secondary endpoints will be assessed by chi-square or Fisher's exact test for categorical variables or t-test or Mann-Whitney-U-test for continuous variables.
 
All tests will be conducted on a two-sided significance level of alpha = 0.05.
 |

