| Assessment of asthma control (GINA)                         |        | x                             | x                         |            | x           |                      | x           |                      |             |                      | x                      |
| Adverse events (AE)                                                     |        | x                             | x                         | x          | x           | x                    | x           | x                    | x           | x                    | x                      |
| Concomitant therapy                                                     |        | x                             | x                         | x          | x           | x                    | x           | x                    | x           | x                    | x                      |
| Trial completion                                                        |        |                               |                           |            |             |                      |             |                      |             |                      | x                      |

1. Hematology and blood chemistry. Topical (percutaneous) analgesia to reduce pain associated with venipuncture, e.g. amethocaine gel or EMLA cream (Eutectic Mixture of Local Anesthetics), must be applied (may only be omitted in patients who explicitly refuse it). A maximum of 3 puncture attempts to obtain blood (approx. 5 mL) will be performed. Visit 1 laboratory parameters comprise: differential blood count, glutamate-pyruvate-transaminase (GPT), glutamate-oxalate-transaminase (GOT), alkaline phosphatase (AP), urea, creatinine levels and total serum IgE and specific IgE to birch, grass, *Dermatophagoides pteronyssinus*, *Alternaria*, *Cladosporium*, cat, dog, hen's egg, cow's milk and peanut. All parameters will be documented in the electronic Case Report Form (eCRF). PaxGene tubes for miRNA will only be sampled at V1.
2. Spirometry/ Oscillometry will only be performed in children  $\geq 4$  years who are capable of providing spirometry / oscillometry of acceptable quality. To confirm acceptable quality, spirometry / oscillometry measurements will be performed in patients  $\geq 4$  years if they are capable of providing measurements of acceptable quality (with a mouthpiece) and if the required equipment is available at site.

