### 8.1 Sample size

Sample size calculations were based on results published by Vrijlandt E et al. (33). In this study, children aged 1–5 were treated with Tiotropium 5 µg vs placebo as add-on to ICS. After 105 days, 29% of the Tiotropium 5µg group had an asthma exacerbation with pneumonia or asthma worsening, whereas 55.9% of the placebo group had an event. For the present study, it can be assumed that most patients treated with ICS + placebo will suffer from one severe exacerbation within one year, therefore a rate of 90% of placebo patients with a severe exacerbation after one year is anticipated. For the Tiotropium group, a rate of 75% is assumed. The estimation of the difference in rates between the placebo and the Tiotropium group is performed conservatively, assuming a smaller difference than observed after 105 days in the study of Vrijlandt E et al (33). The assumed dropout rate of 15% is converted into a group-loss hazard (0.16) and considered in the sample size calculation. With an event rate of 90% in the control group and 75% in the Tiotropium group and a drop-out-rate of 15%, the sample size will amount to 152 patients when applying a two-sided log-rank test with a hazard ratio of 0.60, a significance level of  $\alpha = 0.05$  and a power of 0.8. The power calculation was performed with PROC POWER in SAS® 9.4.

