### 8.3.1 Definition and analysis of primary endpoint

The primary analysis is the comparison of time to first severe exacerbation within 12 months of therapy between groups. This means especially that observations after 12 months will be censored. Dropouts because of lack of efficacy will be considered as an exacerbation. All other dropouts will be censored. The comparison will be done on a two-sided significance level of  $\alpha = 5\%$ .

The primary hypotheses are:

$$H_0: h_E/h_C = 1 \quad \text{versus} \quad H_1: h_E/h_C \neq 1$$

Where  $h_E$ ,  $h_C$  are the hazards in the experimental treatment group and the control treatment group respectively.

The time to first severe exacerbation will be analyzed by Cox regression with factor treatment group and the covariates age group and center assuming a constant hazard ratio over time. The constant hazard ratio assumption will be checked by Schoenfeld residuals. The primary analyses will be performed in the ITT population. Treatment differences will be displayed by estimates of the hazard ratios and 95% confidence intervals.

Several sensitivity analyses will be performed. The primary analysis Tiotropium + at least ICS versus placebo + ICS will be repeated additionally adjusted for LABA and LTRA use. This analysis is not primary since LABA use is not treatment independent. Additional covariates might be considered in the Cox model as well as the assessment of the per-protocol effect (both specified in the SAP). A time to recurrent event analysis is also performed. Since a substantial correlation between the events is expected a Prentice Williams and Peterson (PWP) model with the age group and center will be employed. Additionally, a Kaplan-Meier analysis including a Kaplan-Meier plot will be done.

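### The primary Cox model does not adjust for baseline eosinophils and sensitization, which the protocol calls predictive of exacerbation; adding them would be a cheap gain in efficiency, not the repair of an error

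*Protocol*

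**What the plan says.** - **Prognosis.** Protocol 1.1 states: "Sensitization and eosinophils are useful in the prediction of future exacerbation". The same sentence goes on to say that these markers may pick out the children who benefit most from daily ICS.
- **Tiotropium.** Later in 1.1: "Tiotropium has been shown to be efficacious regardless of IgE levels and blood eosinophils".
- **Measurement.** Footnote 1 of the Trial Schedule puts a differential blood count and "total serum IgE and specific IgE to birch, grass" and eight further allergens at visit 1. Section 5 lists the laboratory tests at visit 1 and randomization at visit 2. No age limit is set on the blood sample.
- **Planned use.** The synopsis and sections 3.4, 6.1 and 8.3 list eosinophils, IgE and specific IgE as possible biomarkers of treatment response. All but the synopsis place them under the endpoints for children aged 4 and older.
- **Primary model.** Synopsis: "The time to first severe exacerbation will be analyzed by Cox regression with factor treatment and the covariates age group and center". Section 8.3.1 repeats this.
- **Further covariates.** Section 8.3.1, in the paragraph on sensitivity analyses: "Additional covariates might be considered in the Cox model", to be specified in the SAP.

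**The concern.** The protocol names two baseline variables as predictors of the event that the trial counts, and collects both before randomization. Its primary model uses neither. Because the covariates of the primary model are stated twice, this is a choice made in the protocol and not a detail left to the SAP. Section 8 adds that a major change to the primary analysis also needs a protocol amendment.

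The point bears on power because most children are expected to have an event. In a Cox model with many events, omitting a prognostic covariate moves the estimated treatment hazard ratio towards 1, and the test loses some power. That power could be recovered without more patients or measurements. Randomization is also unstratified (3.5.1), so a chance imbalance in a marker would go uncorrected in the primary test.

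**Working it through.** **Inputs from the protocol.** Section 8.1: 12-month event rates of 90% (placebo) and 75% (tiotropium), "two-sided log-rank test with a hazard ratio of 0.60", power 0.80, 15% dropout, N = 152. Section 8.3.1: censoring at 12 months. Synopsis: "All tests will be conducted on a two-sided significance level of alpha = 0.05". The allocation ratio is not stated; 1:1 is assumed.

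**Step 1: reproduce the planned sample size.**
- Placebo hazard: −ln 0.10 = 2.303 per year.
- Hazard ratio implied by the rates: ln 0.25 / ln 0.10 = 0.602, which matches the stated 0.60.
- Loss hazard: −ln 0.85 = 0.1625, which matches the stated 0.16.
- Events needed (Schoenfeld): 4 × (1.960 + 0.842)² / (ln 0.60)² = 120.3, so 121.
- Probability of an observed event, h/(h + g) × (1 − exp(−(h + g))), with g the loss hazard: 0.855 on placebo (h = 2.303) and 0.704 on tiotropium (h = 0.60 × 2.303 = 1.382). The mean is 0.779.
- N = 121 / 0.779 = 155.3, so 156. The Lakatos log-rank method also gives 156. The stated 152 is 4 lower, which is within 3%.
- At N = 152 about 152 × 0.779 = 118.4 events are expected. Power = Φ(√(118.4/4) × 0.511 − 1.960) = Φ(0.82) = 0.79.

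The plan therefore has close to its stated power before any marker is considered.

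**Step 2: gain from one prognostic covariate.** The protocol gives no hazard ratio for either marker, so a range is assumed. Trials of 152 children were simulated (6,000 per setting) with overall 12-month rates held at 90% and 75%, loss hazard 0.1625, and a Wald test at two-sided 5%.

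| Assumed marker | Power without | Power with | Gain (points) |
|---|---|---|---|
| HR 1.2 per SD | 79.6% | 80.9% | 1.2 |
| HR 1.3 per SD | 80.3% | 83.1% | 2.7 |
| HR 1.5 per SD | 82.0% | 88.2% | 6.2 |
| HR 1.75 per SD | 84.3% | 93.1% | 8.8 |
| HR 2.0 per SD | 85.0% | 96.5% | 11.5 |
| Yes/no, 40% positive, HR 1.3 | 78.7% | 79.0% | 0.3 |
| Yes/no, 40% positive, HR 1.5 | 78.9% | 81.2% | 2.3 |
| Yes/no, 40% positive, HR 2.0 | 80.4% | 85.1% | 4.7 |

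Gains were taken from unrounded powers. At HR 1.5 per SD, the treatment hazard ratio within marker levels is 0.561; the model without the marker estimates 0.588 and the model with it 0.557.

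**Step 3: age group already in the model.** With the marker correlated 0.5 with age (4,000 trials per setting), the gains are 1.3 points (HR 1.2 per SD), 4.8 (1.5), 7.5 (1.75) and 9.2 (2.0). Age group carries part of the signal but not all of it.

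**Step 4: both markers together.** A separate simulation assumed 40% sensitized and a normally distributed eosinophil score. The model had treatment alone, or treatment plus the two markers.

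| HR sensitized; HR per SD of eosinophils | Power without | Power with |
|---|---|---|
| None | 79.5% | 79.1% |
| 1.3; 1.15 | 80.0% | 81.2% |
| 1.5; 1.2 | 80.9% | 83.3% |
| 2.0; 1.3 | 82.4% | 88.8% |

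The standard error of one simulated power is √(0.8 × 0.2 / 6000) = 0.5 point, so the loss of 0.4 point in the first row is hardly more than noise. Under the null hypothesis this marker-adjusted model rejected in 5.1% to 5.6% of trials. That figure does not describe the full model: once age group and 13 center terms are included, the rejection rate is above 6% whether or not the markers are in it, mainly because of the center terms.

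**The case against.** The strongest reply is that nothing here is wrong. A prespecified Cox model with age group and center is valid, and choosing two more covariates is a matter of preference. That stands, and the point is put forward as an improvement only.

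A second reply concerns the size. The sentence that calls the markers predictive also ties them to ICS response, and ICS is required for every child (3.6.2 and Table 1 in 4.2). If marker-positive children start at higher risk but gain more from ICS, the markers may say little about risk while on ICS. This also stands. It is why the gain is stated only under assumed hazard ratios, and why the low end of the range deserves weight.

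Three stronger readings are tempting, but the documents do not support them.

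- **That the trial is underpowered because of the omission.** The stated hazard ratio of 0.60 follows from the overall event rates (Step 1), so any dilution by unmeasured or omitted predictors is already inside the planning figure. In the settings above, the model without the markers keeps about 79% to 85% power. Large losses appear only if 0.60 is read as the effect within marker levels, and section 8.1 does not derive it that way.
- **That the plan uses the markers the wrong way round.** Efficacy across IgE and eosinophil levels does not rule out a difference in the size of the effect, and that sentence does not name sensitization. Exploring response biomarkers in an age group with few data is legitimate and contradicts nothing in section 1.1.
- **That the SAP could settle the matter unaided.** Section 8.3.1 leaves further covariates to the SAP only for sensitivity analyses. Using them in the primary test means changing the protocol.

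**Conclusion.** The point holds as forgone efficiency. The primary model leaves out two baseline variables that the protocol itself calls predictive and already collects. The planned analysis is sound without them.

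The gain is about 1 to 9 points of power if a marker has a hazard ratio of 1.2 to 1.75 per SD. It is under 1 point for a weak yes/no marker, and turns into a loss of about 0.4 point if the markers have no prognostic value. These figures rest on assumed prognostic strengths, proportional hazards, complete marker data and 1:1 allocation. None of the strengths can be checked from the protocol. The case for the change is the asymmetry: a possible gain of several points against a loss of a fraction of a point.

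**What to change.** In the synopsis and section 8.3.1, by amendment before unblinding, and then in the SAP:

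1. Add two covariates to the primary Cox model besides age group and center: visit 1 blood eosinophils (log scale, continuous) and visit 1 sensitization (at least one of the ten specific IgE tests positive, yes/no).
2. Fix one missing-value rule that is blind to treatment, for example the overall mean for a missing value plus a missing indicator, so that every child in the ITT population stays in the analysis.
3. Report the model without the markers as a sensitivity analysis.

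The biomarker endpoints can stay as they are.

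The cost is an amendment and a few sentences; no new data are needed. Some toddlers will have no blood result, since puncture attempts are limited to three, and the simulations did not include missing values. The model gains a few terms, so its type I error should be checked by simulation with age group and center included. The adjusted hazard ratio is an effect within marker levels, and the report should say so.
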